### Phase 2: Randomized Controlled Trial

#### Hypothesis

We hypothesize that virtual world CR users will improve behaviors (physical activity, diet, and smoking) to a greater degree than conventional CR participants.

#### Recruitment

Potential participants hospitalized for an ACS or those undergoing elective PCI procedures will be identified from the Division of Cardiovascular Diseases Hospital service census (coronary care unit, general and ischemic ward services, interventional service) by the study team cardiovascular clinical nurse specialist. Each patient will be approached prior to dismissal as part of CR discharge planning during which time they will be provided with pertinent information on the purpose and requirements of the study. Following eligibility screening by the nurse specialist, they may choose to provide written informed consent at the time of recruitment or at another convenient time (ie, baseline visit). Furthermore, eligible patients will be recruited from the Mayo Clinic outpatient CR enrollment listings. Efforts will be implemented to increase priority population (ethnic minorities, rural residents, elderly, and economically disadvantaged) accrual including community-based strategies, clinician-initiated recruitment, advertisements, and medical record review.

#### Baseline Visits

All participants will undergo an outpatient, baseline assessment for collection of sociodemographics, medical history, prescribed medications/adherence [39], smoking status, surveys for heart disease knowledge [40], diet quality [41,42], physical activity patterns [43,44], self-efficacy [41,44,45], social support/influence [46], and physical and mental health-related quality of life [47] utilizing validated instruments after obtainment of written informed consent. Clinical assessments including anthropometrics (height, weight, body mass index, waist circumference, and blood pressure) and laboratory studies (lipid panel, blood glucose, and hemoglobin A1c) will be obtained by standard protocols and/or extracted from participant medical records from their ACS index hospitalization or follow-up medical visits. As a part of the standard clinical CR intake process, all participants will undergo an oxygen consumption exercise treadmill test (ETT) to assess for heart rate and blood pressure responses and exercise capacity. All participants will attend an in-person computer and device training session similar to that carried out during the feasibility study and will receive a personal laptop and headset for use during the study (both control and intervention groups for standardization). Participants will also receive a personal activity tracker (Fitbit^TM^ ) as a tool to accurately assess free-living physical activity [48]. Participants will be asked to wear the activity trackers on a daily basis and to upload their data to a secure webserver at least once weekly. Each participant will receive a binder of education materials (including slide presentations) relevant to their respective assignment.

#### Design and Randomization

The study will consist of a 2-arm, parallel group, single-center RCT. Patients will be randomized at a 1:1 ratio by a computer software-generated list (nQuery advisor) at their baseline outpatient CR visit to adjunct virtual world-based CR with conventional CR or conventional CR only. Randomization will be stratified by block sizes of four.

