#### Enhanced Virtual World-Based Intervention

In addition to standard center-based CR, the intervention group will have access to an interactive healthy lifestyle community, *Destination Rehab*, delivered through a virtual world platform on Second Life. The platform will provide specialized educational tools on CVD secondary prevention including information on nutrition, physical activity, smoking, medication adherence, etc. Specific program components will include interactive 3D spaces (ie, grocery store, fitness center, restaurant, virtual library, and human heart tour), and live Mayo Clinic health professional-led education sessions and peer discussion forums (ie, social support groups) (see Figures 1-4) [31-34]. The platform design has the intention of encouraging healthy lifestyle behaviors by participant avatars with the goal of transferring these behaviors to the real world (ie, Proteus effect) [26,28, 51]. The platform features were informed by valuable input from the Mayo Clinic patient and family advisory group (One Voice) at focus groups in January and February 2014, and will be further developed from Phase 1 study results. Weekly education sessions, including slide presentations, will last for 60-90 minutes and allow for interaction between the facilitators and participants through voice chat and text message features (see Multimedia Appendix 1). A summary of the proposed education sessions including key patient-centered elements for promotion of healthy lifestyle change is provided in Textbox 1 [49,50].

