### Sample Size Estimation and Power Calculations

Power analysis for a priori sample size was performed with equivalence testing for two proportions in a randomized design using the program nQuery advisor. Using data on previous research, we estimated that 45% of patients receiving conventional CR, and 74% of patients attending *Destination Rehab* with conventional CR would have at least one correction of a cardiovascular behavioral risk factor at 12 months [29]. Therefore, to discover a clinically-relevant difference of this size between the groups at a 0.05 alpha level with 80% power, we will require 50 participants per group. Assuming a drop-out rate of 10%, we aim to recruit a total of 120 patients for the RCT.

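### The randomisation sentence confuses blocking with stratification, and a fixed, published block of four leaves up to a third of assignments predictable

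*Protocol article*

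**What the plan says.** All references are to the Protocol article, Phase 2.

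- **Design and Randomization**, on the design: "The study will consist of a 2-arm, parallel group, single-center RCT". On the method: "Patients will be randomized at a 1:1 ratio by a computer software-generated list (nQuery advisor) at their baseline outpatient CR visit". On restriction of the list: "Randomization will be stratified by block sizes of four". No stratification factor is named here or elsewhere in the article.
- **Baseline Visits**: "Each participant will receive a binder of education materials (including slide presentations) relevant to their respective assignment". The materials therefore reveal the arm.
- **Enhanced Virtual World-Based Intervention**: "In addition to standard center-based CR, the intervention group will have access to an interactive healthy lifestyle community". The control arm has no counterpart to these live sessions, and no masking is described.
- **Recruitment**, on eligible patients: "they may choose to provide written informed consent at the time of recruitment or at another convenient time (ie, baseline visit". Consent can therefore fall at the same visit as randomisation.
- **Sample Size Estimation and Power Calculations**: "Assuming a drop-out rate of 10%, we aim to recruit a total of 120 patients for the RCT".

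**The concern.** The sentence has two defects.

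First, it does not say what it appears to say. Stratification means separate lists within levels of a baseline factor; blocking means forcing balance after every so many patients. The sentence uses the first word for the second idea. Whoever generates the list cannot tell whether strata were intended and left out or whether blocking was misnamed.

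Second, the blocking it does specify is small, fixed and public. Where staff can see which arm earlier patients received, they can work out some coming assignments from the block size alone. Concealing the list does not prevent this, because the information comes from past assignments and not from the list. If the next arm is known before a patient has consented, the decision to enrol, or when to enrol, can depend on it. The arms may then differ in ways that adjustment for measured baseline variables corrects only in part.

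**Working it through.** **Inputs.** Allocation 1:1, block size 4, one centre (Design and Randomization); 120 patients (Sample Size Estimation and Power Calculations), that is 120/4 = 30 complete blocks. The article gives no predictability figure to reproduce. The observer is assumed to know the block size and to see every earlier assignment in the same list.

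**Step 1: assignments known with certainty.** A block has six equally likely orders: AABB, BBAA, ABAB, ABBA, BABA, BAAB. An assignment is certain once two patients in the block have received the same arm.

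- AABB and BBAA: positions 3 and 4 are certain, 2 assignments each.
- The other four orders: only position 4 is certain, 1 assignment each.
- Mean per block = (2×2 + 4×1)/6 = 8/6 = 4/3.
- Share = (4/3)/4 = 1/3. Of 120 patients: 120 × 1/3 = 40.

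**Step 2: best-guess success.** The rule is to guess the arm with more places left in the block.

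| Position | Probability that the guess is right |
|---|---|
| 1 | 1/2 |
| 2 | 2/3 |
| 3 | (1/3)×1 + (2/3)×(1/2) = 2/3 |
| 4 | 1 |

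Mean = (1/2 + 2/3 + 2/3 + 1)/4 = 17/24 = 70.8%. Of 120 patients: 120 × 17/24 = 85 correct guesses, against 60 by chance.

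**Step 3: what other block schemes achieve.** Fixed sizes are enumerated exactly as above. Varying sizes come from 2,000 simulated lists of 120. There the observer knows the candidate sizes and all past assignments, but not which size was drawn for each block.

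| Scheme | Certain | Best guess right |
|---|---|---|
| Fixed 4 (as stated) | 33.3% | 70.8% |
| Fixed 6 | 25.0% | 68.3% |
| Fixed 8 | 20.0% | 66.6% |
| Varying 4/6 | 5.5% | 69.2% |
| Varying 4/6/8 | 2.2% | 67.9% |

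Of 120 patients, certain assignments fall from 40 to 120 × 0.055 = 6.6 (sizes 4/6) or 120 × 0.022 = 2.6 (sizes 4/6/8). Best-guess success changes little.

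**Step 4: cost in balance.** The largest possible difference in arm sizes is half the largest block. That is 4/2 = 2 at any moment with fixed fours (0 after 30 complete blocks), and 8/2 = 4 with sizes up to eight. With two strata it could reach 4 + 4 = 8.

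**Step 5: where foreknowledge could act.** Inpatients are approached and screened before dismissal, while randomisation comes later at the outpatient baseline visit. At screening, a patient's place in the list is not yet fixed, so the coming arm is generally unknown. At the baseline visit the place is fixed, and under Recruitment consent may still be outstanding. That is the point of exposure.

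**The case against.** The strongest reply is that the figures describe an ideal observer. The article does not say that the screening nurse specialist randomises patients, hands out the binders or sees earlier allocations. Deferred consent is an option, not the rule. Patients cannot see the sequence, activity and diet come from validated questionnaires, and the authors call the study a pilot. A condensed article may also leave concealment and stratification factors to the full protocol.

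Most of this stands, and it rules out several stronger readings that a reader might infer:

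- *That the list is unstratified.* The article shows a defective sentence and no named factor. It does not show that no strata exist. If they do, the wording is still wrong, and the one-third figure applies within each stratum to someone who tracks strata separately.
- *That baseline smoking decides which components of the composite a patient can achieve.* Under Measures, a nonsmoker meets the smoking component by staying one and a smoker by quitting, so both can meet all three. Only the abstract's shorter wording, which mentions cessation alone, suggests otherwise. Smoking status is likely prognostic, and that is a weaker claim.
- *That 40 patients will be selectively enrolled, or that inpatient screening or questionnaire scoring is compromised.* Nothing in the article supports this.
- *That concealment is missing.* An article may leave it out, and its absence is not counted here.

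What the reply does not remove is the sentence itself, the fixed published size, and consent that may coincide with randomisation. Calling the study a pilot lowers the stakes, but Phase 2 is powered for a between-arm comparison and the change is nearly free.

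**Conclusion.** The point holds in limited form and should be corrected before Phase 2 begins. The sentence confuses blocking with stratification and names no factor. As stated, the design leaves up to one third of assignments (40 of 120) certain and 71% of best guesses right. Both figures are exact for 1:1 blocks of four.

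They rest on two assumptions: that the observer knows the block size, which the article publishes, and that the observer sees every earlier assignment in the list. That the trial is open is inferred from visibly different arms and the absence of any masking statement; the article does not use the word. The figures bound the opportunity for selection. They do not estimate bias in the primary outcome, and the article gives no basis for such an estimate.

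**What to change.** Replace the sentence under Design and Randomization with wording to this effect:

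*Patients will be randomised 1:1 in permuted blocks of randomly varying size. Block sizes will not be disclosed to recruiting staff. Randomisation will take place only after written consent and all baseline assessments are complete.*

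Sizes 4, 6 and 8 would serve, but the sizes used should be kept from recruiting staff and out of published text.

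Then settle the word stratified: delete it, or name the factor. Baseline smoking status (current smoker, yes or no) is a reasonable optional choice. It is already collected at baseline, and it is likely to predict the composite because a smoker must quit to meet the component that a nonsmoker meets by staying one. If it is used, adjust for it in the primary analysis.

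The gain should not be oversold. Varying sizes nearly remove certain knowledge of the next assignment, but best-guess success stays at about 68 to 69%. Placing randomisation after consent and baseline assessments keeps the actual assignment from being revealed before either is finished.

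The cost is one new computer-generated list and the slightly larger possible imbalance shown in the working, with no added visits or staff. The abstract reports that only Phase 1 is recruiting, so no randomised patient is affected.

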#### Control Conventional Cardiac Rehabilitation Program

The control group will enroll in a standard center-based CR program, which at Mayo Clinic Rochester consists of 36 sessions over a duration of 12-16 weeks. The comprehensive program includes supervised exercise, cooking demonstrations, didactic lectures, video presentations, group support, and stress management sessions. Participants will have face-to-face access to the medical directors, registered dietician, exercise physiologist, case manager, and stress management specialist. The curriculum course topics and sessions developed according to national standards of care for secondary prevention are outlined in Textbox 1 [49,50].

#### Enhanced Virtual World-Based Intervention

In addition to standard center-based CR, the intervention group will have access to an interactive healthy lifestyle community, *Destination Rehab*, delivered through a virtual world platform on Second Life. The platform will provide specialized educational tools on CVD secondary prevention including information on nutrition, physical activity, smoking, medication adherence, etc. Specific program components will include interactive 3D spaces (ie, grocery store, fitness center, restaurant, virtual library, and human heart tour), and live Mayo Clinic health professional-led education sessions and peer discussion forums (ie, social support groups) (see Figures 1-4) [31-34]. The platform design has the intention of encouraging healthy lifestyle behaviors by participant avatars with the goal of transferring these behaviors to the real world (ie, Proteus effect) [26,28, 51]. The platform features were informed by valuable input from the Mayo Clinic patient and family advisory group (One Voice) at focus groups in January and February 2014, and will be further developed from Phase 1 study results. Weekly education sessions, including slide presentations, will last for 60-90 minutes and allow for interaction between the facilitators and participants through voice chat and text message features (see Multimedia Appendix 1). A summary of the proposed education sessions including key patient-centered elements for promotion of healthy lifestyle change is provided in Textbox 1 [49,50].

#### Measures

The primary outcome is a composite including improvement of at least one of the following 3 cardiac risk factors at baseline, 3, 6, and 12 months (1) physical activity (at least 150 minutes per week), (2) diet (consumption of five or more fruits and vegetables daily), and (3) smoking (complete cessation for baseline smokers, maintained nonsmoking status for baseline nonsmokers). Secondary outcomes will include improvement in all 3 cardiac risk factors, intention and self efficacy to achieving lifestyle change [41,44,45], change in exercise capacity by peak oxygen uptake (VO_2_), change in weight (≥5% weight reduction for patients with baseline BMI >30 kg/m^2^), blood pressure optimization (blood pressure <140/90 mmHg, <130/80 mmHg for diabetics), diabetes control (hemoglobin A1c<7%), hyperlipidemia control (low-density lipoprotein <100 mg/dL), medication adherence [39], social support/influence [46], physical and mental health-related quality of life [47], heart disease knowledge [40], and user evaluation of the virtual world platform (satisfaction, usability, and utility) [22,35-38].

Physical activity will be assessed by the International Physical Activity Questionnaire (IPAQ) which determines physical activity patterns (vigorous-intensity, moderate-intensity, and leisure) over the previous seven days [43]. Furthermore, free-living physical activity data will be obtained from personal activity trackers as number of steps per day [48]. All patients will undergo a symptom-limited ETT with oxygen consumption testing to assess for peak VO_2_ [52,53]. Continuous blood pressure and heart rate measurements, as well as electrocardiograms will be obtained during exercise and recovery periods. A brief dietary recall by a food frequency questionnaire will allow for diet evaluation [42]. Mayo Clinic laboratories will process and analyze all fasting blood specimens including lipid panel (total cholesterol, triglycerides, high density lipoprotein cholesterol, and low density lipoprotein cholesterol), blood glucose, and hemoglobin A1c. Physical examination measures including height, weight, body mass index, waist circumference, and blood pressure will be obtained according to standard guidelines and Mayo Clinic protocols [54-55]. The baseline questionnaires and clinical assessments will be repeated at 3, 6, and 12 months (study completion).

At program completion, we also plan to have semi-structured focus groups to solicit feedback on the intervention and control rehabilitation programs. We anticipate holding at least two sessions (one for each study group) with at least 20 participants per session. We will collect information on participant experiences, attitudes, and beliefs on healthy lifestyle change through open-ended intervention questions developed by the research team. Incentives for participating in the program and for completion of follow-up surveys will be provided to participants (proposed gift certificates and the Mayo Clinic Healthy Heart for Life book).

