**Methods:**

In Phase 1, we will recruit at least 10 patients enrolled in outpatient CR who were recently hospitalized for an ACS (unstable angina, ST-segment elevation myocardial infarction, non-ST-segment elevation myocardial infarction) or who recently underwent elective PCI at Mayo Clinic Hospital, Rochester Campus in Rochester, MN with at least one modifiable, lifestyle risk factor target (sedentary lifestyle, unhealthy diet, and current smoking). Recruited patients will participate in a 12-week, virtual world health education program which will provide feedback on the feasibility, usability, and design of the intervention. During Phase 2, we will conduct a 2-arm, parallel group, single-center, randomized controlled trial (RCT). Patients will be randomized at a 1:1 ratio to adjunct virtual world-based CR with conventional CR or conventional CR only. The primary outcome is a composite including at least one of the following (1) at least 150 minutes of physical activity per week, (2) daily consumption of five or more fruits and vegetables, and (3) smoking cessation. Patients will be assessed at 3, 6, and 12 months.

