## Methods

### Study Setting and Participants

We will recruit patients who were recently hospitalized for an ACS (unstable angina, ST-segment elevation myocardial infarction, non-ST-segment elevation myocardial infarction), or who recently underwent elective percutaneous coronary intervention (PCI) at Mayo Clinic Hospital, Rochester Campus in Rochester, MN with at least one modifiable, lifestyle risk factor target: sedentary lifestyle (<3 hours of physical activity per week), unhealthy diet (consumption of <5 servings of fruits and vegetables daily), and current smoking (>1 year). All patients must have regular high-speed Internet access (either home, work, or community). Patient exclusion criteria will include less than 18 years of age, enrolled in a current CR program, and non-fluent in English. The feasibility research protocol was reviewed and approved by the Mayo Clinic Institutional Review Board and the randomized controlled trial (RCT) will be registered. We include details of the design and methods of both the feasibility study and the proposed RCT as Phases 1 and 2, respectively.

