### Statistical Analysis

#### Quantitative Data

For normally distributed variables, simple arithmetic means and standard deviations will be calculated. For categorical variables, frequencies and proportions will be calculated. For clinical endpoints, we plan to calculate changes in measures by comparing differences in change from baseline to follow-up interval. We will include sensitivity analyses with the inclusion of patients with complete data only. Analyses will be performed using commercial software (SAS version 9.2, SAS institute), and a two-tailed value of *P*<.05 as statistically significant.

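### As written, the Phase 2 primary composite counts a nonsmoker who stays a nonsmoker as a success, which contradicts the improvement it claims to measure and the correction on which the sample size rests

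*Protocol article*

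**What the plan says.** The Measures section of Phase 2 in the protocol article states: "The primary outcome is a composite including improvement of at least one of the following 3 cardiac risk factors". The components are physical activity of at least 150 minutes per week, five or more fruits and vegetables daily, and "smoking (complete cessation for baseline smokers, maintained nonsmoking status for baseline nonsmokers".

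Three other places bear on this:

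- **Study Setting and Participants** admits patients "with at least one modifiable, lifestyle risk factor target: sedentary lifestyle" (under 3 hours of activity per week), unhealthy diet, or current smoking. Any one is enough, so a nonsmoker can enter on diet or inactivity alone.
- **Abstract, Methods** gives the last two components as "daily consumption of five or more fruits and vegetables, and (3) smoking cessation". Maintained nonsmoking does not appear there.
- **Sample Size Estimation and Power Calculations** says "we estimated that 45% of patients receiving conventional CR, and 74% of patients attending" the virtual world programme with conventional rehabilitation "would have at least one correction of a cardiovascular behavioral risk factor at 12 months". It concludes that "at a 0.05 alpha level with 80% power, we will require 50 participants per group".

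**The concern.** Under a one-of-three rule, a component that a patient meets by staying as they were decides that patient's outcome. A nonsmoker who enters with a poor diet, keeps the poor diet, stays inactive and does not start smoking meets the primary outcome as the Measures section words it. That holds equally in both arms, so these patients add successes to both arms and almost nothing to the difference.

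The primary outcome and the sample size then describe different events. The calculation concerns correction of a risk factor, whereas the Measures definition also rewards a factor that never needed correction. If the Measures wording is followed at analysis, control success rises, the difference shrinks, and 50 per arm no longer gives the stated 80% power.

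**Working it through.** **Step 1. Reproduce the plan's figure.** The inputs from the sample size section are 45% versus 74%, alpha 0.05, 80% power and 50 per group. The Quantitative Data section specifies "a two-tailed value of" P<.05, so the test is taken as two-sided. The usual two-proportion formula gives 44 per arm without continuity correction and 51 with it. At 50 per arm, power is 80.5% by Fisher's exact test and 86% by the chi-square test (exact binomial enumeration). The stated 50 is reproduced, so the calculation is sound for the event it describes.

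**Step 2. Check whether 45% is compatible with the Measures definition.** Let q be the nonsmoker share, and assume that 95% of nonsmokers stay nonsmokers. Control success is then at least 0.95q, even if nobody else succeeds. Setting 0.95q = 0.45 gives q = 0.45/0.95 = 0.474. Above about 47% nonsmokers, a 45% control rate cannot occur under this definition.

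**Step 3. Apply the Measures definition.** The documents do not give the smoker share s, so it is varied. The assumptions are that 95% of nonsmokers stay nonsmokers and that all other patients (smokers, and nonsmokers who start) succeed at r = 0.45 in control and r = 0.74 in intervention:

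p = (1 − s)(0.95 + 0.05r) + s·r

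For s = 0.30:

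- Control: 0.70 × 0.9725 + 0.30 × 0.45 = 0.6808 + 0.1350 = 0.816
- Intervention: 0.70 × 0.9870 + 0.30 × 0.74 = 0.6909 + 0.2220 = 0.913

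The difference between arms is 0.29 × [s + 0.05(1 − s)]. For s = 0.30 this is 0.29 × 0.335 = 0.097, instead of the planned 0.29.

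**Step 4. Power of the two-sided chi-square test (exact enumeration).** Sixty per arm is the full 120 with no dropout.

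| Smokers (assumed) | Control | Intervention | Power, 50 per arm | Power, 60 per arm |
|---|---|---|---|---|
| Planned rates | 45% | 74% | 86% | 91% |
| 90% | 50.2% | 76.5% | 79% | 86% |
| 70% | 60.7% | 81.4% | 64% | 73% |
| 50% | 71.1% | 86.3% | 47% | 54% |
| 30% | 81.6% | 91.3% | 31% | 34% |
| 20% | 86.8% | 93.8% | 21% | 25% |

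With 10% dropout from 120 (120 × 0.9 / 2 = 54 per arm), power at 90% smokers is 82%.

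**Step 5. Sensitivity.** If every nonsmoker stays one, the pooled normal approximation at 50 per arm gives 78%, 62%, 44%, 26% and 18% for the same five smoker shares. The 95% figure is not what drives the result.

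**The case against.** The strongest reply is that the sentence requires improvement, and staying a nonsmoker is not improvement. On that view the parenthesis exists only so that nonsmokers can be scored on the secondary outcome of improvement in all three factors, where it makes sense. This is a fair reading and may be what was intended. But the parenthesis sits inside the definition of the primary outcome and says what the smoking component means for baseline nonsmokers. The sentence contradicts itself, and either reading needs an edit.

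A second reply is that 45% and 74% might already include maintained nonsmoking. They come from a cited source that is not at hand, so this cannot be excluded outright. The wording of the sample size section speaks against it, and Step 2 confines it to samples in which nonsmokers are a minority.

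A reader might also infer that most patients would succeed without any change, or that the trial could not detect a behavioural effect at all. The documents support neither. The first needs a nonsmoker majority, and no smoker share is given. The second overlooks that smokers still contribute to the contrast, and that the all-three-factors outcome and the activity and diet data are kept. With few nonsmokers the loss is small: at 90% smokers, power is 79% with 50 per arm and 86% with 60.

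**Conclusion.** The point stands as an internal contradiction in the primary endpoint. The Measures wording lets a nonsmoker succeed with no behaviour change. It disagrees with its own word improvement, with the abstract, and with the event used for the sample size. It should be corrected before Phase 2 starts.

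How much power is lost depends on the case mix, which the documents do not state. Across 90% down to 20% smokers, power at 50 per arm runs from just under 80% to about one in five, and recruiting the full 120 without dropout recovers only part of it. These figures rest on the assumed 95% maintenance and on equal 45% and 74% rates for all patients who do not succeed by maintained nonsmoking.

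**What to change.** Define primary success as at least one behavioural risk factor that was deficient at baseline being at target at 12 months. Smoking then counts only for baseline smokers, through complete cessation. Take maintained nonsmoking out of the primary composite and keep it only for scoring the secondary outcome on all three factors. Use the same wording in the abstract, the Measures section and the sample size section, so that 45% versus 74% refers to the endpoint analysed.

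One further rule is needed. Eligibility defines sedentary as under 3 hours (180 minutes) per week, but the activity target is 150 minutes. A nonsmoker with an adequate diet who does 150 to 179 minutes per week is eligible yet already at target, and would have no factor to correct. Either reconcile the two thresholds or state how such patients are classified.

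The cost is protocol wording plus that classification rule. Smoking status, diet and activity are already collected at baseline and at 3, 6 and 12 months, so no new data are required.
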